# The multifactorial approach and the food allergen-specific substitutive diet as a tool to manage and ameliorate adverse reactions to foodstuffs in adulthood: study protocol for a randomized controlled trial—the ALASKA study

**DOI:** 10.1186/s13063-024-08307-2

**Published:** 2024-07-20

**Keywords:** Clinical trial, Diet, Disease management, Food hypersensitivity, Food intolerance, Nutrition therapy

## Abstract

**Background:**

Adverse reactions to foodstuffs (ARFS), specifically food allergy (FA) and food intolerance (FI), are increasing worldwide and represent a major public health concern. Thus, ARFS management, its identification, evaluation, and intervention, must provide a comprehensive solution.

**Objectives:**

(a) To develop a multifactorial strategy for ARFS management in adults with FA and/or FI; (b) to describe the multiple influential variables in ARFS within the realm of ARFS management; and (c) to design a personalized food allergen-specific substitutive diet (FASSD), as a 6-month dietary treatment option for adults with ARFS and as a component of ARFS management.

**Methods:**

The ALASKA study will consider the following main variables as part of the ARFS management: (1) demographics and clinical information; (2) symptomatology, food and beverages intake and physical activity; (3) hematobiochemical study; (4) immunology; (5) enzymatic activity; (6) anthropometry, body composition, and physical fitness; (7) QoL; (8) 6-month intervention; (9) end of the study; and (10) other assessments. The FASSD will be designed with special emphasis on the commonly lacking micronutrients in the ARFS population: niacin, Mg, K, P, Ca, Zn, B12, folate, Fe, and fiber.

**Discussion:**

The ALASKA study protocol has been developed as a global strategy to manage and evaluate ARFS in Spanish adults older than 18 years of age. Approaching ARFS with multiple assessments, as influencing factors, will lead to a novel strategy for ARFS management. The FASSD has been designed as a personalized tool to avoid crucial micronutrient deficiencies that a current strict food allergen avoidance or elimination diet may provoke.

**Trial registration:**

The protocol has been approved by the Ethics Committee of the UPM (REF.20200602) and registered on ClinicalTrials.gov (NCT05802017).

**Supplementary Information:**

The online version contains supplementary material available at 10.1186/s13063-024-08307-2.

## Introduction

Adverse reactions to foodstuffs (ARFS) are based on an individual’s specific response to food components and have been generally classified by pathogenic mechanism of action and attributed mostly to food allergy (FA) and/or food intolerance (FI) (Fig. 1) [1]. Currently, more than 150 million Europeans suffer from chronic allergic disease, including about 20 million suffering from FA and more than 80 million from FI [2, 3]. Prevalence of ARFS, especially the ones related to FA and FI, has been increasing over the past decades in developed and developing countries becoming an important public health concern [4]. Given that the reactions to foodstuffs are often regarded as pediatric problems, these reactions have not been studied in-depth in adults and no accurate strategies focusing on this population have been established. It has been estimated that by 2050, 50% of the world’s population will be affected by at least one type of allergy; and as one in every five people globally will be aged 60 years or over by that time, the general health and quality of life (QoL) of the adult population emerges as an essential object of study for the coming years [5].

**Fig. 1 Fig1:**
[figure not shown]
Adverse reactions to foodstuffs classification updated and adapted from a selected literature (described below). Adapted from: Immune-mediated reactions: [6–9]; Non-immune-mediated reactions: [7, 10, 11]

The *gold standard* to diagnose immune-mediated and non-immune-mediated reactions to foodstuffs is the oral food challenge (OFC) [12]. However, to avoid procedures that may imply a prolonged regular practice, there are short breath tests available, such as the Cerascreen® Lactose/Fructose hydrogen H_2_ and methane CH_4_ breath test kit (Cerascreen GmbH, Schwerin, Germany). Similarly, there are clinically relevant blood biomarkers, such as specific immunoglobulins (mostly food-specific IgE antibody (Ab) reactions for type I hypersensitivity or type I food allergy (T1FA)), that together with a clinical history of symptoms can help in diagnosis [13, 14]. In addition, other physical and clinical tests might also contribute to the clarification of the study of specific populations, such as athletes, who may present different physical activity levels (PAL). The presence of ARFS in individuals with particular symptomatology could be linked to gastrointestinal, skin, and/or nervous system (NS) conditions, specifically when having type II hypersensitivity or type II food allergy (T2FA) [15, 16].

In fact, T2FA has been one of the most recently and newly explored hypersensitivities as a tool in the development of ARFS research. Figure 1 outlines the ARFS classification according to the pathogenic mechanism of action. The clinical relevance of food-specific IgG_4_ Ab in food allergy is currently unclear and not recommended to be used alone as a food allergy predictor. It has been observed that IgE/IgG_4_ ratios can be used to enhance the diagnostic and prognostic performance of sIgE [17].

Current treatments of ARFS are not optimal nor ideal from the nutritional and physical condition point of view. For T1FA, treatment consists of strict food allergen avoidance and the use of adrenaline (for allergen-induced systemic reactions), epinephrine, and/or a 24-h dietary recall tool [18]. The application of treatments such as strict food allergen avoidance may cause nutritional deficiencies in certain cases of multiple food allergen responses due to the avoidance of important food groups. For instance, milk avoidance in adults may result in calcium deficiency [19] and lower intakes of zinc and vitamin B2. Likewise, prolonged gluten-free diet make individuals prone to the development of, most notably folate deficiency and lower intakes of calcium, iron, zinc, folate, and fiber; affecting their nutritional status and altering the intestinal microbiota [20]. Substitutive diets suggesting the replacement of allergy-related food for allergen-free food have shown symptoms’ score improvement. Hence, the 6-month intervention of the ALASKA study, to manage and ameliorate ARFS in adulthood, consists in the implementation of a general nutritional advice with dietary recommendations for a healthy lifestyle for subjects in the control group; and a 6-month food allergen-specific substitutive diet (FASSD) for subjects in the intervention group. These effects are greater in subjects with specific pathologies: atopic dermatitis [21], urticaria [22], and gastrointestinal disorders [23].

Consequently, a novel strategy involving the assessment of multiple variables and a FASSD to manage and ameliorate ARFS is proposed in this study. The aim of this study is (a) to develop a multifactorial strategy for ARFS management in adults with FA and/or FI; (b) to describe the multiple influential variables in ARFS within the realm of ARFS management; and (c) to design a personalized FASSD, as a 6-month dietary treatment option for adults with ARFS and as a component of ARFS management.

## Materials and method

### Study design

This will be a randomized controlled trial (RCT), the Allergies and Food Intolerances in Adults and Athletes study (ALASKA study), with matched pair trial design, exploratory framework, and a 1:2 allocation ratio between the control (Group A) and the intervention group (Group B) respectively, conducted in the Universidad Politécnica de Madrid (UPM) located in the Region of Madrid, Spain. The flow diagram of this study is shown in Fig. 2. The following chart meets The Standard Protocol Items: Recommendations for Interventional Trials (SPIRIT) [24].

**Fig. 2 Fig2:**
[figure not shown]
Flow diagram of the ALASKA study. ARFS: adverse reactions to foodstuffs; FASSD: food allergen-specific substitutive diet; M1: physical and clinical assessments at month 1; M5/6: physical and clinical assessments at month 5 or 6; PSIMP-RAA-10: Pathologies and Symptomatology Questionnaire associated with Adverse Reactions to Foodstuffs; y: years of age

### Participants

#### Recruitment

Volunteers with signs, symptoms, and/or diagnosed diseases related to ARFS and older than 18 years, including men and women, will be recruited. The recruitment period will be active for approximately 1 to 3 months and according to the enrollment response. Enrollment mass e-mail campaigns, social media, digital display screens in public areas of the UPM, and the local online contact flyer/website (https://short.upm.es/kwgpo) of the ImFINE Research Group (ImFINE-RG) will be used to recruit interested adults to participate in the ALASKA study. The first approach with possible participants will take place with the use of phone informative conversations between the researcher and the possible participant to share a wider vision about the trial. Engaged participants will be registered in the study and an anonymous participant code will be assigned (see the “ Data storage” section). Participants will initially complete and sign the Informed consent form (Appendix 1), the Inclusion and exclusion criteria form (Appendix 2), the Demographics and clinical characteristics form (Table 3), and the Pathologies and Symptomatology Questionnaire associated with Adverse Reactions to Foodstuffs (PSIMP-RAA-10). After completing these initial questionnaires, participants will be enrolled and their data will be checked for eligibility by a researcher of the ALASKA study. If extra measures are needed to recruit a sufficient number of participants, the recruitment period will be expanded and all the steps of the recruitment phase will be repeated (expected enrollment rate of approximately 150%). Participants will not receive any economic compensation for volunteering in this study, but they will receive personalized nutritional advice and individual reports of all the performed clinical and physical measurements.

The Research Electronic Data Capture Platform (RedCap®), hosted in the Supercomputing and Visualization Center of Madrid Community of the UPM (CESVIMA-UPM) will be used to digitally secure and perform all types of communication, whether massive or individual. RedCap® platform is a specialized tool to build and manage clinical trials and their corresponding databases. All questionnaires and documents (including Appendix 1, Appendix 2, Table 3, the PSIMP-RAA-10 questionnaires, and any other) that will be used during the ALASKA study will be uploaded and will be shared to participants, when applicable, via the RedCap® platform.

#### Sample size and missing data

The required sample size with 95% of power was calculated using the G*Power software v. 3.1 (Heinrich-Heine-Universität Düsseldorf, Düsseldorf, Germany) [25] and previously related-published data [15] and datasets [16]. The cross-sectional study requires a sample size of *n* = 154 (*d* = 0.3, *α* = 0.05). Meanwhile, the longitudinal study requires a sample size of *n* = 33 for the control group and *n* = 65 for the intervention group (*d* = 0.8, *α* = 0.05).

Even if the participants have agreed to join the ALASKA study voluntarily and signed the informed consent form, they will be allowed to abandon the study at any time, without having to provide a specific argument or being penalized (loss to follow-up, missing data, dropout, or similar). Likewise, the researchers of this study reserve the right to end any participation, according to each researcher’s criteria, for the benefit of the research study (e.g., injuries, long trips, low commitment, outbreak of severe diseases, or similar). Due to the nature of the dietary interventions, modifying allocated interventions is not foreseen in this study. However, if a subject chooses to discontinue the intervention on their own or if the researcher decides to stop a participant's intervention for any reason, it will be documented in each participant's individual case report and in the End of Study Form (Annex VIII). Subjects will be able to explain, or not, the reason for voluntarily abandoning the study.

#### Data storage

Participants’ alphanumeric codification will be assigned in RedCap® adopting the format “ALXXXX” (two static letters, pointing the study name, ALASKA study, and four random-digit unique code). Complete records of each participant will be stored in RedCap® platform, locally hosted in the CESVIMA-UPM. Digital databases of each assessment and instrument will be created promoting the data quality and avoiding the need of duplicating questionnaire measurements. Databases will be locked using a secure password and with access to the coordinator and principal investigator (PI) of the ALASKA study ([name], [name]). Additional researchers, after the authorization of the PI ([name]), will have also access to the password and the study databases. [name] will make final decisions regarding the RedCap® platform management, trial supervision, and the trial start/termination point. RedCap® platform provides the “Data Exports, Reports, and Stats” module, which allows to view reports, inspect plots and descriptive statistics of the data, at any point/time of the trial, as well as export data to Microsoft Excel, SAS, Stata, R, or SPSS for analysis (if access provided by [name] to the researchers of the Alaska study). Complete individual records will be documented using the unique and anonymous participant code and will not contain identifiable participants’ information. Routine day-to-day audits; weekly back-ups of the datasets; and monthly internal audits of the available services (water and electricity) and resources (laboratory equipment) will be performed to support data quality.

Subjects of the study will be selected according to the following described inclusion and exclusion criteria and if they have completed the required preliminary questionnaires: Informed consent model (Appendix 1), Inclusion and exclusion criteria form (Appendix 2), and the Pathologies and Symptomatology Questionnaire associated with Adverse Reactions to Foodstuffs (PSIMP-RAA-10) [14].

#### Inclusion criteria

Enrolled participants who will accomplish the following inclusion criteria will be eligible subjects of study: (1) participants without a pacemaker, prosthetic devices, or metal implants; (2) participants with availability of time to attend two venous blood sample extractions and to dedicate at least 30 min to complete online questionnaires related to this study; (3) participants with the possibility, and not restricted by medical advice, of fasting for at least 8 h (for the extraction of blood samples) and doing physical exercise (including the physical capacity of going up and down stairs); (4) participants that, during physical exercise, have not experimented any chest pain, chest stiffness-tightness, or dizziness; (5) participants who have not had a cardiac arrest, angina pectoris or heart failure; and (6) participants with equal or greater than 6-score signs, symptoms or diseases using the previously validated PSIMP-RAA-10 tool [14].

#### Exclusion criteria

Participants with the following conditions will be excluded from the study: (1) being simultaneously involved in another research study; (2) heavy smokers (> 25 cigarettes/day), according to The Aspect Consortium of the European Commission classification scales [26]; (3) pregnant women; (4) receiving drug therapies with any type of antibiotic, antidepressant, sleeping pill, or anti-anxiety medication, or participants who will need to change their drug treatment protocol during the study; (5) previous diagnosis of coeliac disease (CeD), FA and/or FI, eating disorders, or infection due to the *Helicobacter pylori* bacteria during the last year; (6) participants with a job or lifestyle that potentially interferes with their regular sleep schedule (e.g., night shift and on-call); (7) participants with some type of major surgery that involves having been hospitalized during the last 5 years, including current muscle injuries and muscle cramps; (8) suffering from any type of cancer or other fatal illness within the last 5 years; (9) participants who are not willing to continue and finish the study for any reason; and (10) participants who, according to the researchers’ criteria, cannot continue the study (e.g., injuries, long trips, low commitment, outbreak of severe diseases, or similar).

#### Randomization

The ALASKA study will follow a sample randomization using the RedCap® randomization automated tool (RRAT) for the study allocation of subjects. RRAT assigns subjects by chance (rather than by choice) into specific groups (Group A and Group B) and monitors the overall allocation progress and assignment of randomized subjects. It is not possible to blind subjects or staff in this study from the tested treatment due to nutritional interventions which will be used as dietary treatments for the management of ARFS. Nevertheless, the outcome assessors will be blinded to the group assignment given the use of anonymized participant codes among all the steps of the study.

#### Allocation

Subjects will be randomly placed in Group A (control), or Group B (intervention) in a 1:2 allocation ratio using the RRAT tool. RRAT tool access will be granted to the outcome researchers of the Alaska study. The duration of the study for both control and intervention groups will be between 5 and 6 months. Individuals assigned to the control group will receive general nutritional advice with dietary recommendations for a healthy lifestyle (Annex I), while subjects assigned to the intervention group will receive a personalized food allergen-specific substitutive diet or FASSD (Annex II).

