## Symptomatology, food and beverages intake, and physical activity

The validated Pathologies and Symptomatology Questionnaire associated with Adverse Reactions to Foodstuffs (PSIMP-RAA-10); and Food and Beverages Frequency Consumption Questionnaire to Identify Adverse Reactions to Foodstuffs (FBFC-ARFSQ-18) tools will be used to record the clinical picture (diseases, signs and symptoms) and the food frequency consumption of the subjects of study [14]. Additionally, hydration status will be assessed using the Hydration Questionnaire of the ImFINE Research Group (IMFINE-HYD) to record water and other beverage intake [33]. Besides, food and beverages record will be measured through a 24-h dietary recall interview (24HDRI) (Annex III). Medication and food supplement intake will be also assessed in this interview. The daily energy and nutrient intake of each participant will be calculated by using DIAL software [34], which works with food composition databases such as the Spanish Food Composition Database (BEDCA) and the United States Department of Agriculture Food Composition Database (USDA-FCD), among others. Additionally, to encourage subjects to follow the assigned 6-month intervention and promote the dietary treatment adherence, all subjects will be contacted monthly during the study using a Dietary Adherence Questionnaire (Annex IV, authors’ own creation, based on questions of previously published validated questionnaires [35] and adapted to the 6-month intervention). Subjects will be asked to maintain their normal physical activity habits during the time of the study, from M1 to M5/6.

The International Physical Activity Questionnaire Long Form (IPAQ-LF) [36] and the Rapid Assessment of Physical Activity (RAPA) [37] will be administered to determine the minutes per week of self-reported physical activity and the physical activity scores of the study sample, respectively. Using the IPAQ-LF, evaluations are made according to the types of physical activities that people do as a part of their daily lives (walking, moderate to severe information about time spent in activities, and time spent sitting). The energy required will be calculated with the MET (metabolic equivalent)-minute scores.

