### Quality of life

The self-perceived health-related QoL of the subjects of study will be assessed using the validated tools: Short-Form Health Survey 12 (SF-12) and the Spanish validated version of the Food Allergy Quality of Life Questionnaire—Adult Form (S-FAQLQ-AF).

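### The assessor-blinding claim rests on participant codes that do not hide allocation, and is apparently contradicted by giving outcome researchers access to the randomisation tool

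*Protocol article*

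**What the plan says.** Four statements in the protocol article bear on this.

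- **Randomization**, on participants and staff: "It is not possible to blind subjects or staff in this study from the tested treatment".
- **Randomization**, on assessors, as an exception to that: "the outcome assessors will be blinded to the group assignment given the use of anonymized participant codes among all the steps of the study". No other means of blinding is given.
- **Randomization**, on the REDCap randomisation tool (RRAT): it places participants in Group A or Group B by chance and "monitors the overall allocation progress and assignment of randomized subjects".
- **Allocation**, on who may use the tool: "RRAT tool access will be granted to the outcome researchers of the Alaska study". No restricted view and no separation of roles is described.

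The outcome sections show how each outcome is obtained. The symptom and food-frequency questionnaires "will be used to record the clinical picture (diseases, signs and symptoms) and the food frequency consumption of the subjects of study". Physical activity is self-reported through two questionnaires. On quality of life, the text reads "The self-perceived health-related QoL of the subjects of study will be assessed using the validated tools". Blood count, biochemistry, antibody and body-composition results are read by analysers or devices.

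**The concern.** A claim of blinded outcome assessment tells the reader that the person measuring or scoring an outcome could not be influenced by knowing the arm. In an open-label dietary trial, that claim is the main protection the staff-obtained outcomes have against detection bias. Here the only stated basis does not deliver it, and the next section appears to give allocation access to the people who handle outcomes.

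If the claim is carried into the results paper unchanged, readers will give blinded status to measurements that may not have had it. They may also extend it to questionnaire outcomes that no assessor blinding can cover. The article names no primary outcome, so the reader cannot set the problem aside as touching only secondary measures.

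**Working it through.** No figure in the article tests this point. The check sets the statements side by side.

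**Step 1. What the code does.** The Data storage section describes a study prefix followed by four random digits, assigned in REDCap. This replaces the participant's name. It carries no information about the arm, but it does not stop anyone who can look up the arm for that code. It protects confidentiality and does not mask allocation.

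**Step 2. What the tool shows.** By the Randomization section, RRAT makes the assignment and keeps track of it. A user with access can therefore be expected to see the arm for each participant, unless the view is restricted. The article mentions no restriction.

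**Step 3. Who has the tool.** The Allocation section gives access to the outcome researchers. The term is not defined and is not distinguished from outcome assessors.

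**Step 4. The two possible readings.**

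| Relation between the two roles | Consequence for the blinding claim |
|---|---|
| Same people, or overlapping | Contradicted: those said to be blinded can open the record of assignments |
| Entirely different people | Not contradicted, but the protection would come from separating the roles, which the article does not state. The code still does not provide it |

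The stated justification fails on both readings. The contradiction depends on the first, which is the more natural one.

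**Step 5. Which outcomes the claim could cover at best.**

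| How the outcome is obtained | Examples in the article | Could assessor blinding apply? |
|---|---|---|
| Reported by the participant | Symptom, food-frequency, physical activity and quality-of-life questionnaires | No. The participant is in effect the assessor and knows the arm |
| Interview | 24-hour dietary recall | Only in part: the interviewer could be blinded, but the participant answering is not |
| Staff-run physical measurement | Handgrip, chair test, step test, waist-hip ratio | Yes, if the person measuring has no access to allocation |
| Analyser or device reading | Blood count, biochemistry, antibodies, impedance | Yes, and it is plausible if coded material is handled by people without access |

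The claim can therefore be true only for the last two rows and the interviewer's part of the second. Even there, it depends on an access arrangement that the article does not describe.

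**The case against.** The strongest reply is that the two role names are never equated. Outcome researchers could be a separate group who run the randomisation, and a journal article may leave detailed roles and user rights to the full protocol. The first part stands: a reader might infer that no blinding exists at all, and the documents do not support that. Staff processing coded samples on analysers may well not know the arm. The second part does not rescue the text, because the article does not leave the mechanism open. It names one, and that one does not work.

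A second reply is that the article openly says participants are unblinded, so self-report contradicts nothing. That is correct. Self-report limits how far the claim reaches; it does not make the article inconsistent.

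Four further inferences are tempting and should not be drawn.

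- *All physical-fitness and body-composition outcomes are compromised.* The article does not say who takes these measures. Several are tightly standardised: the step test is submaximal, with fixed height, pace and duration, and body composition is read by a device.
- *Results by arm are open to all.* The Data storage section says the REDCap reporting module "allows to view reports, inspect plots and descriptive statistics of the data, at any point/time of the trial", but this describes what the software can do. The same section locks the databases by password, requires the principal investigator's authorisation for further researchers, and does not mention reports by arm.
- *Allocation knowledge drives eligibility or withdrawal decisions.* No text links the researchers who take those decisions to RRAT access, or says that upcoming assignments are visible.
- *The bias can be sized against the planned effect of d = 0.8.* The documents give no basis for any size of expectation or coaching effect, and d = 0.8 is tied to no named outcome.

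**Conclusion.** The point holds in this form: the assessor-blinding statement is unsupported by the reason given for it, is apparently contradicted by the access granted in the next section, and cannot extend to participant-reported outcomes. This is an error in what the article states, not a detail left to a fuller document.

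Its size is a matter of scope. Blinded status is unavailable for symptoms, food frequency, physical activity and quality of life. It is unverified for interview, staff-run and analyser-read outcomes until access is disclosed.

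The contradiction assumes that outcome researchers and outcome assessors overlap, and that RRAT access shows individual assignments. The failure of the code-based justification needs neither assumption.

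**What to change.** 1. **Access.** Remove RRAT access, and visibility of the allocation field, from anyone who still measures, interviews for, scores or analyses outcomes. Analysts can receive the arm once scoring and data-cleaning decisions are closed. Keep access with existing staff who do not assess outcomes.
2. **Text of the Randomization section.** Replace the code-based justification with a statement that the blinding claim covers only outcomes measured by staff without RRAT access, and list those outcomes. Bring the Allocation section into line by defining outcome researchers and saying how they relate to outcome assessors.
3. **Disclosure.** State who held RRAT access during the month 5/6 assessments, and whether any of them measured, interviewed or scored.
4. **Labelling.** Describe participant-reported outcomes as unblinded, together with any staff-measured or interview outcome taken by someone with RRAT access.

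The cost is a change of REDCap permissions and a few sentences, with no extra staff if existing roles can be kept apart. The Trial status section says that recruitment finished in May 2023 and that fieldwork was expected to end by July 2024, the month of publication. Item 1 can therefore help only with assessment, scoring and analysis still to be done. Items 2 to 4 remain useful whatever the timing.
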